### Data collection and data management

By embracing the Findability, Accessibility, Interoperability and Reusability of digital assets principles, we underscore our commitment to robust, transparent and ethically sound scientific practices that advance research integrity and propel scientific progress. Using the Leiden University Medical Centre (LUMC) Data Management Tool, with the support of the LUMC section of Advanced Data Management, we ensure that our data are findable, enabling easy discovery through well-structured metadata and standardised identifiers. Through our commitment to accessibility, we guarantee that both researchers and the broader community can access our data with minimal barriers, fostering collaboration and knowledge dissemination. Interoperability remains a focal point, as we structure our data in standardised formats and use established vocabularies, facilitating seamless integration with other datasets and tools. Our dedication to reusability ensures that the data generated through our trial can be leveraged beyond its initial purpose, promoting long-term scientific impact and innovation.

Data collection is done in standardised electronic databases. All relevant clinical data will be entered into electronic Case Report Forms. Data storage and backup will be managed by the Castor Electronic Data Capture (EDC) system. Data will be managed confidentially and coded in compliance with the European Union General Data Protection Regulation. Castor’s encryption module will be used for pseudonymisation. All analyses will be performed on de-identified, pseudonymised, coded data, for which explicit permission is given in the patient informed consent form. A subject identification code list will be used to link the data to each subject when needed for data collection. Once assigned, the number will not be reused if the patient is excluded. After completion of the study, the key file will be archived in the hospital’s study documentation in a protected location on the network hard drive for 15 years in accordance with Article 17 of the European Good Clinical Practice Directive.

The LUMC is the trial sponsor and will have access to the final dataset. A clinical trial agreement is distributed among the other participating centres.

### Sample size calculation

In studies of both chronic and acute pain, a change of two points on the NRS has been shown to be clinically relevant and correlated to a patient’s need to take additional pain medication.^38^ To detect a minimal clinically important difference of two points on the NRS, considering an SD of 3.5 from similar studies that measured pain at one time point after 12 months^15 23 26 27^ in a clinically heterogeneous group, with a significance level of 0.025, we need to analyse 2×76=152 patients to achieve 90% power. With an estimated loss to follow-up of 6%, we need to include 162 patients. Moreover, based on the study by Cascini *et al*^25^ and our clinical experience, we expect a 1-year mortality rate of 20% in our patient population aged 75 years or younger. With an estimated 1-year survival of this patient group of 80%, we need to include 203 patients in total. Due to the semiacute setting of most amputations, organising the availability of both extra operating time and a trained nerve surgeon might be a challenge. Therefore, we estimate including 40% of all major lower extremity amputations. To be able to randomise 203 subjects, we estimate the need to screen 508 patients (figure 2).

**Figure 2 F2:**
[figure not shown]
Consolidated Standards of Reporting Trials (CONSORT) flow diagram of predicted patient inclusion.

### Randomisation, blinding and treatment allocation

The Randomisation Module within Castor EDC will be used to assign participants to specific groups (web-based randomisation/treatment allocation system). In this way, an unpredictable allocation sequence will be generated so that the treatment allocation is concealed from the patient, nurses and rehabilitation professionals. Simple randomisation is used to reduce the risk of selection and accidental bias. Randomisation will not be stratified by centre because of the risk of selection bias due to treatment predictability in centres with low inclusion rates. Furthermore, due to the anticipated low inclusion rate in some centres, an imbalance in the number of patients per study arm can be created when working with stratification by centre. Therefore, randomisation will be global over all participating centres. Patients will be blinded to the allocation until the end of the study, 1 year after the last patient is included.

### Statistical analysis

Continuous variables will be summarised by treatment group using the number of non-missing data points, mean, SD, median and IQR. Categorical and ordinal variables will be summarised by treatment group based on observed frequencies and percentages relative to the total number of non-missing items. To account for the correlation between measurements within the same patient, a repeated measures analysis will be conducted. This will allow us to include all participants with at least a single follow-up measurement. Where appropriate, we will include age, sex and amputation level in our analyses.

#### Primary study parameter(s)

We selected four co-primary endpoints on the basis of the expected impact of the intervention and relevance for the patients. They are all primarily assessed at 12 months after surgery:

RLP (NRS).PLP (NRS).PROMIS Pain Behaviour Short Form (7 a).PROMIS Pain Interference Short Form (8 a).

These outcomes will be compared between the two treatment groups on the basis of the intention-to-treat principle. The comparisons will be adjusted for age, sex and amputation level, based on clinical relevance. To account for multiple comparisons, we proceed as follows. We start by testing outcomes 1 and 2 at a significance level of 0.025 (two-sided) using the Bonferroni correction. This is the basis of our sample size calculation. Next, we apply a serial gatekeeping procedure:

If both outcomes 1 and 2 reach statistical significance, outcome 3 will be tested at a significance level of 0.05 (two-sided). If outcome 3 reaches statistical significance at that level, outcome 4 will be tested at a significance level of 0.05 (two-sided).If either outcome 1 or 2 reaches statistical significance, outcome 3 will be tested at a significance level of 0.025 (two-sided). If outcome 3 reaches statistical significance at that level, outcome 4 will be tested at a significance level of 0.025 (two-sided).^39^

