### Study procedures

After randomisation, patients will receive general anaesthesia without a muscle relaxant for the TMR group. Intraoperative epidural anaesthesia is not allowed as this will reduce nerve conduction, making nerve stimulation less dependable. The amputation will be performed by a qualified vascular surgeon or a senior resident in training under supervision. The skin will be incised using a fishmouth incision (transfemoral and through-knee) and according to Burgess’ technique (transtibial). If patients are randomised in the TMR group, a trained nerve surgeon will perform the nerve coaptation. Postoperative protocol is similar for both interventions, including the use of analgesia. In transfemoral and through-knee amputations, there will be an additional 10-centimetre incision on the posterior side of the leg. This additional incision is necessary to coaptate the sciatic nerve. To ensure proper blinding, a sham skin incision will be performed in the control group. Closure and dressing of the wound will be similar between groups.

To ensure homogeneity in all participating centres a treatment and postoperative care protocol will be distributed for both the intervention and control groups (online supplemental file 3), in addition to a central cadaver-based TMR course.

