### Benefits and risk assessment, group relatedness

The additional risks of performing TMR during an amputation are negligible. TMR can be performed at any level of the lower extremity with a standardised technique. For TMR to be possible in transfemoral and through-knee amputations, an additional sham incision (around 10 cm) must be made on the dorsal side of the leg, medial to the sartorius muscle. To properly blind study participants, this additional incision must also be superficially performed for the transfemoral and through-knee amputations in the control group. In our experience, this will not result in increased postoperative pain or difficulty sitting.

The surgery time for a standard transtibial and transfemoral amputation will be 45–90 min, depending on the surgeon’s experience. The TMR procedure will add 30–90 min to the surgery.^17^ This extra time investment will rely on technical aspects related to the level of amputation and the surgeon’s experience. Although an increase in surgical time of this length is related to a slightly higher risk of infection, Deeyor *et al*^18^ did not find more complications in patients who had acute TMR compared with the standard of care. Deeyor *et al* found a 77% complication rate in the primary TMR group, compared with 87% in the amputation-only group.^18^ There is a small chance of failure of the TMR procedure.^40^ If patients suffer harm from trial participation, the LUMC provides participant insurance for potential financial compensation.

The burden of the study is acceptable, as participation only requires patients to complete several questionnaires at five evaluation time points. This will translate to about 2 min at 2 weeks, 14–21 min at 3, 6 and 9 months and 20–29 min at 12 months postamputation. Additionally, participants will fill out a daily questionnaire consisting of 2 questions about pain for 30 consecutive days at 11 months postamputation. Patients who fail to complete the questionnaires in 2 weeks will receive an automatic reminder and a call from the researcher to promote participant retention.

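### The stated models ignore clustering by nerve surgeon, who operates in the TMR arm only, so the 0.025 tests can be anti-conservative

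*Protocol article*

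**What the plan says.** All references are to the Protocol article.

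- **Primary model** (Primary study parameter(s)): "The comparisons will be adjusted for age, sex and amputation level, based on clinical relevance". Secondary study parameters names the same three covariates.
- **Correlation modelled** (Statistical analysis, opening paragraph): a repeated measures analysis, whose stated purpose is to handle correlation within a patient. No model that is described contains nerve surgeon or centre.
- **Who operates** (Study procedures): a vascular surgeon, or a supervised senior resident, amputates in both arms. Then: "If patients are randomised in the TMR group, a trained nerve surgeon will perform the nerve coaptation". No nerve surgeon is described for the control arm.
- **Allocation** (Randomisation, blinding and treatment allocation): simple and individual. "Randomisation will not be stratified by centre because of the risk of selection bias", with predictability in low-recruiting centres as the reason.
- **Error control** (Primary study parameter(s)): "We start by testing outcomes 1 and 2 at a significance level of 0.025 (two-sided) using the Bonferroni correction". Outcomes 3 and 4 are tested only if this first step succeeds.
- **Sample size** (Sample size calculation): "we need to analyse 2×76=152 patients to achieve 90% power", with no allowance for clustering.

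**The concern.** This is a partially nested design: patients in one arm are grouped by the operator who delivers the experimental procedure, and patients in the other arm are not. A model that treats patients as independent once age, sex and amputation level are accounted for leaves between-surgeon variance out of the standard error of the treatment difference.

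The document gives some reason to expect operator variation. The introduction says that amputation surgeons do not routinely perform TMR. The TMR group section treats size mismatch at the coaptation as a main criticism and scores it. The risk section accepts that the procedure can fail.

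Two things are at stake. Residual and phantom limb pain at 0.025 are the gate to the two PROMIS outcomes, so an inflated first step carries through the procedure. The budget impact analysis also assumes 50% to 100% national implementation, so the result is meant to apply to surgeons beyond those in the trial. For that inference, surgeon variance belongs in the standard error.

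**Working it through.** **Inputs from the document.** Difference of 2 NRS points ("To detect a minimal clinically important difference of two points on the NRS"), SD 3.5 ("considering an SD of 3.5 from similar studies that measured pain at one time point after 12 months"), two-sided alpha 0.025, 76 analysed per arm.

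**Inputs that are assumptions.** Number of nerve surgeons k = 5 to 20, and surgeon ICC = 0.01 to 0.10. The document gives neither.

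**Step 1: the plan's own figure.** The SE under independence is 3.5 × √(2/76) = 0.568, so the standardised effect is 2/0.568 = 3.523. The critical value is 2.2414. Power = Φ(3.523 − 2.2414) = 0.900 (0.895 with the t distribution). Inflation: 152/0.94 = 161.7, so 162; 162/0.80 = 202.5, so 203. The plan's figures reproduce under independence, with no design effect.

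**Step 2: clustering in the TMR arm only, equal caseloads.**

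- Patients per surgeon: m = 76/k
- Design effect in the TMR arm: DE = 1 + (m − 1) × ICC
- True SE / planned SE: r = √((DE + 1)/2)
- Actual alpha of the planned test: 2 × (1 − Φ(2.2414/r))
- Power of the planned test: Φ((3.523 − 2.2414)/r)
- Power of a test that uses the correct SE: Φ(3.523/r − 2.2414)

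| Surgeons (m) | ICC | DE | r | Actual alpha | Power, planned test | Power, correct SE |
|---|---|---|---|---|---|---|
| 20 (3.8) | 0.01 | 1.028 | 1.007 | 0.026 | 0.898 | 0.896 |
| 20 (3.8) | 0.10 | 1.280 | 1.068 | 0.036 | 0.885 | 0.855 |
| 10 (7.6) | 0.02 | 1.132 | 1.032 | 0.030 | 0.893 | 0.879 |
| 10 (7.6) | 0.05 | 1.330 | 1.079 | 0.038 | 0.882 | 0.847 |
| 10 (7.6) | 0.10 | 1.660 | 1.153 | 0.052 | 0.867 | 0.792 |
| 5 (15.2) | 0.05 | 1.710 | 1.164 | 0.054 | 0.864 | 0.784 |
| 5 (15.2) | 0.10 | 2.420 | 1.308 | 0.087 | 0.836 | 0.674 |

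The last two columns describe different tests. The inflated alpha goes with the planned test, and the lower power goes with the corrected one. The last column uses the normal critical value, so small-sample degrees of freedom would lower it somewhat.

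At 10 surgeons and ICC 0.05, restoring 90% power at the same caseload per surgeon would need about 76 × (1.33 + 1)/2 = 88.5, so 89 analysed per arm.

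**Step 3: unequal caseloads, by simulation.** An unadjusted two-group t-test was applied to 152 patients under simple randomisation, with 20,000 runs per setting and a surgeon effect in the TMR arm only. From 15 down to 5 surgeons, type I error was 0.032 to 0.041 at ICC 0.02, 0.038 to 0.067 at ICC 0.05, and 0.054 to 0.112 at ICC 0.10. At 10 surgeons and ICC 0.05, the mean model SE was 0.575 against an empirical 0.646. Unequal caseloads therefore make the problem somewhat larger than the table shows.

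**Step 4: centre, by the same simulation.** With a centre effect common to both arms (5 to 15 centres of unequal size, ICC 0.05 to 0.20) and centre left out of the analysis, type I error was 0.023 to 0.027 against 0.025. At 10 centres and ICC 0.10, the model SE was 0.564 and the empirical SE 0.563. The standard error is valid.

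**The case against.** The strongest reply is that this article condenses a fuller protocol, that the SAP is not shown, and that random-effects structure is usually settled there. Naming three covariates and a repeated measures analysis does not rule out a surgeon term. This stands as a caution: the SAP may already deal with the point. It does not remove it, because the article states which covariates and which correlation are modelled, and its sample size assumes independence.

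Second, the size is assumed throughout. A common treatment protocol and a central cadaver course (Study procedures) may keep the ICC low, and at the mild end the effect is negligible. This stands, and is why only a range is given.

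Third, operators act in both arms, so controls may cluster too. But the vascular surgeons serve both arms. To the extent that their effects are common to both, those effects behave like a centre effect and do not distort the SE. The nerve surgeon has no counterpart among controls.

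Some stronger readings are tempting but unsupported:

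- **That not stratifying by centre makes standard errors too small.** Step 4 shows that it does not. Chance imbalance between centres is already covered by the error rate, and the document gives its reason for not stratifying.
- **That few surgeons deliver TMR.** The document says that availability is limited, but gives no count.
- **That the plan concedes that pain depends on surgeon experience.** The sentence "This extra time investment will rely on technical aspects related to the level of amputation and the surgeon’s experience" is about operating time.
- **That the planned test drops to 85% or 79% power.** Those figures belong to a test with the correct SE. At 10 surgeons and ICC 0.05 the planned test keeps about 88%, but at an actual alpha of about 0.038.
- **That the surgeon's identity is already on file.** Nerve handling is documented, but no section says that the operator is.

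**Conclusion.** The point holds for the nerve surgeon and not for centre. The design puts an operator effect in one arm only, and the stated models have no term for it. If pain at 12 months varies by nerve surgeon, the tests of residual and phantom limb pain are anti-conservative.

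The actual two-sided error is about 0.026 to 0.087 over 5 to 20 surgeons and ICC 0.01 to 0.10. The middle case of 10 surgeons and ICC 0.05 gives about 0.038, and about 85% power for a test that allows for the clustering. These figures rest on an assumed surgeon count and ICC, on equal caseloads, and on the plan's SD of 3.5. That SD comes from single-time-point pain scores, whereas the endpoint averages 30 daily scores and is covariate-adjusted, so the true SD may differ.

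Omitting centre loses some precision and no validity.

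**What to change.** 1. Prespecify a partially nested model, with a random effect for nerve surgeon in the TMR arm only and small-sample degrees of freedom. Use it at least as a sensitivity analysis of residual and phantom limb pain.
2. Confirm that the operating nerve surgeon is recorded for each TMR patient.
3. State the expected number of nerve surgeons and an ICC range, so that the likely effect on error and power can be judged.
4. Add a random intercept for centre to the primary model, for precision only. Simple, unstratified randomisation can stay as it is.

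Centre-clustered standard errors are not a good substitute for item 1, because they are unreliable with few clusters.

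**Cost.** The change is to analysis wording, plus one data field if the surgeon is not already captured. Recruitment is unaffected. The interval will be slightly wider if surgeon clustering exists. If it does not, the variance estimate goes to about zero and the result changes little.

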**Trial registration number:**

NCT06719245. Dutch trial registry: NL87196.058.24

STRENGTHS AND LIMITATIONS OF THIS STUDYThe multicentre, randomised, sham-controlled design minimises potential bias.The study is appropriately powered to detect differences in both phantom limb pain and residual limb pain.The use of multiple validated questionnaires, including patient-reported outcome measures, ensures robust assessment of the treatment effect.The expected inclusion is limited to 40% of eligible patients due to the availability of nerve surgeons and the additional operating time in a semiacute setting.

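### The gatekeeping procedure is valid but needlessly conservative: alpha left after outcome 4 is not returned to the pain outcome that missed 0.025

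*Protocol article*

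**What the plan says.** The Primary study parameter(s) section lists four co-primary endpoints: RLP, PLP, PROMIS Pain Behaviour (outcome 3) and PROMIS Pain Interference (outcome 4). It then sets out the alpha path in full:

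- Start: "We start by testing outcomes 1 and 2 at a significance level of 0.025 (two-sided) using the Bonferroni correction".
- Both pain outcomes succeed: "If both outcomes 1 and 2 reach statistical significance, outcome 3 will be tested at a significance level of 0.05 (two-sided"), and outcome 4 follows at 0.05 if outcome 3 passes.
- One succeeds: "If either outcome 1 or 2 reaches statistical significance, outcome 3 will be tested at a significance level of 0.025 (two-sided"). Then: "If outcome 3 reaches statistical significance at that level, outcome 4 will be tested at a significance level of 0.025 (two-sided").

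No step follows outcome 4. The Sample size calculation derives 76 per arm from 90% power at a significance level of 0.025. The strengths and limitations box says: "The study is appropriately powered to detect differences in both phantom limb pain and residual limb pain".

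**The concern.** Suppose RLP passes at 0.025 and PLP does not. The 0.025 that RLP earned moves to outcome 3 and then to outcome 4. If both pass, only PLP is left untested at a higher level, and half of the 0.05 is spent on nothing. A Bonferroni-based graphical procedure may send that 0.025 back, so that PLP is tested at its own 0.025 plus the returned 0.025, that is 0.05.

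Without the return, a trial in which RLP and both PROMIS outcomes pass at 0.025 and PLP has p = 0.03 must report PLP as not significant, although a rule with the same familywise error would allow the claim. RLP and PLP are the outcomes tested first and the basis of the sample size. The step cannot be added once the results are known.

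**Working it through.** **Inputs.** From the Sample size calculation: difference 2 points, SD 3.5, two-sided alpha 0.025, power 90%, 76 per arm analysed. From the Primary study parameter(s) section: the alpha path above. Assumed, because the protocol does not give them: the correlation between the test statistics (0 to 0.9, equal for all pairs) and the power of each PROMIS outcome at 0.025.

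**1. The plan's own figure.** n per arm = 2 × (z₀.₉₈₇₅ + z₀.₉₀)² × 3.5² / 2² = 2 × (2.241 + 1.282)² × 12.25 / 4 = 76.02. The stated 76 reproduces. So do 152/0.94 = 161.7, rounded to 162, and 162/0.80 = 202.5, rounded to 203.

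**2. Power per pain outcome.** The expected z is (2/3.5) × √38 = 3.523.
- At 0.025: Φ(3.523 − 2.241) = 0.900.
- At 0.05: Φ(3.523 − 1.960) = 0.941.

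**3. Both pain outcomes under the plan.** At correlation 0 this is 0.900² = 0.810. From the bivariate normal it is 0.822, 0.832, 0.847 and 0.869 at correlations 0.3, 0.5, 0.7 and 0.9.

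**4. Adding the return step.** The plan was simulated with and without the step, using four equicorrelated normal test statistics and 1,000,000 runs per scenario. The chance that both RLP and PLP are significant:

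| Correlation | Plan | With return, PROMIS power 90% | Gain at 90% (points) | Gain at 80% (points) | Gain at 50% (points) |
|---|---|---|---|---|---|
| 0 | 0.810 | 0.870 | 6.0 | 4.7 | 1.8 |
| 0.5 | 0.832 | 0.873 | 4.0 | 2.6 | 0.6 |
| 0.7 | 0.847 | 0.879 | 3.2 | 1.7 | 0.2 |
| 0.9 | 0.869 | 0.890 | 2.1 | 0.5 | 0.0 |

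The step can only add rejections, so the gain cannot be negative.

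**5. A weaker effect on one pain outcome.** If the PLP effect is 70% of plan and the other three outcomes have the planned standardised effect, PLP power rises from 0.59 to about 0.67. If the PROMIS effects are also 70% of plan, it rises only to about 0.62.

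**6. Familywise error.** All 15 combinations of true null hypotheses were simulated (400,000 runs each) with very large effects for the rest. With only PLP null, the plan makes a false claim in about 2.5% of trials; with the return step, in about 5.0%. That difference is the unspent alpha. In every combination where more than one hypothesis is null, the two procedures gave the same error rate. The highest value seen in any check was 0.0514, which is within simulation error of 0.05.

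**The case against.** **The procedure is not wrong.** It is valid, and choosing one valid multiplicity procedure over another is a design choice. This stands: the point is lost efficiency, not an error.

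**The return changes how the pain outcomes are read.** As written, the verdict on RLP and PLP never depends on the PROMIS outcomes. With the step, a pain p-value between 0.025 and 0.05 would be significant only if both PROMIS outcomes pass. This also stands as a consequence to accept. It costs no power and no validity.

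**The gain is conditional.** It arises only when exactly one pain outcome passes, both PROMIS outcomes pass at 0.025 and the other pain p-value lies between 0.025 and 0.05. It nearly vanishes with low PROMIS power or high correlation. It is also smaller if the SD proves lower than planned, which is possible: 3.5 comes from studies with a single measurement, whereas this trial averages 30 daily scores and adjusts for covariates. At an assumed SD of 3.0, the chance of both is already about 94% to 95%, and the step adds about 2 points even with PROMIS at the planned standardised effect. At 2.5 it is about 99%, and the step adds less than 0.5 points.

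**A stronger reading the text does not support.** A reader might infer that the strengths statement about both pain outcomes is contradicted by a joint power of 81% to 87%. It is not. The statement names no joint 90%. The sample size section ties 90% to a test at 0.025, and the analysis section names that per-outcome test as its basis. Testing also proceeds if either pain outcome succeeds, so success on both is not the criterion for the trial.

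**Conclusion.** The point holds as a matter of efficiency. The procedure controls familywise error at 0.05 but leaves 0.025 unspent in one branch, where a return to the remaining pain outcome would be valid and would take nothing from outcomes 3 and 4. At the planned effect, the gain in the chance of showing both RLP and PLP is about 2 to 6 points with 90% power for each PROMIS outcome (correlation 0.9 to 0), and about 0 to 2 points with 50%. These ranges rest on assumed correlations and assumed PROMIS power. The case for acting is that the cost is negligible and the opportunity ends at unblinding, not that the gain is large. Reporting the joint power would be a clarification, not a correction.

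**What to change.** Before unblinding, add one rule after the step for outcome 4:

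*If exactly one of outcomes 1 and 2 is significant at 0.025, and outcomes 3 and 4 are both significant at 0.025, the remaining outcome of 1 and 2 is tested at 0.05 (two-sided).*

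This costs one sentence and no patients. The authors should make the choice knowing that the second pain outcome may then depend on the PROMIS results.

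Optionally, say in the strengths box and the Sample size calculation that 90% is the power for each pain outcome, and that the chance of both being significant under the present plan is about 81% to 87% for correlations from 0 to 0.9.
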